### Data and Safety Monitoring

Adverse events will be graded by the investigator using the National Cancer Institute’s “Common terminology criteria for adverse events (NCI-CTCAE v 4.03)” [67]. Information about all adverse events, whether volunteered by the study participant, discovered by the investigator or designee’s questioning, laboratory test or other means, will be recorded and followed as appropriate. The Data and Safety Monitoring Board (DSMB) for this study will comprise one statistician methodologist, one palliative care specialist, and one individual knowledgeable in Natural Health Products for conduct monitoring and supervision of the clinical trial. The DSMB will meet at least once before the study starts and then meet according to the DSMB terms of reference. After every 20th enrolled patient, a trial monitor, who is not part of the research team, will review the trial documentation to ensure that the trial is being conducted according to the trial protocol, the International Conference on Harmonization Good Clinical Practice (ICH GCP), and regulatory requirements.

### Data analysis plan

This feasibility study is not powered to test efficacy. However, we anticipate that it will generate useful data regarding recruitment and retention rates, protocol violation frequency, and some preliminary data on time to onset of first episode of incident delirium during their inpatient admission. These data will further assist in the estimation of sample size for the larger study, as well as its projected duration and cost. Data will be reported regarding the acceptability of the study procedures to patients, families and palliative care unit staff, including pharmacy. The effectiveness of the blinding process will be assessed. Collectively, these outcome data will ultimately determine the feasibility of the larger trial. Although the statistical analysis in this feasibility study will be mainly descriptive, we will also assess time to first episode of incident delirium with a Kaplan-Meier survival analysis. The upper one-sided 95 % limit of median time to onset will also be derived to further guide sample size considerations for the full randomized trial.

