## Background

Delirium is a very common and distressing neuropsychiatric syndrome for patients and their families in palliative care settings [1–3]. Delirium occurrence rates of over 80 % have been reported in the last hours and days before death [4, 5]. Conducting research in this population is challenging and, not surprisingly literature, data are limited owing to patient frailty and high attrition rates in association with the context of advanced disease [6–8].

Delirium is characterized by altered awareness, attention and cognitive deficits, perceptual disturbances, and a fluctuating course with potential intervals of relative lucidity that likely contribute to its underdiagnosis [9]. Delirium impairs patient communication, thus challenging the assessment of pain and other symptoms [1]. It often occurs at a critical juncture in advanced disease, when a preexisting narrow window of opportunity to communicate with family may be further compromised.

Delirium is associated with increases in morbidity, mortality, health care costs and, most importantly, in levels of patient and family distress [10–17]. Increasing age and the presence of dementia are well-known predisposing risk factors for the development of delirium [18]. Given the increasing elderly proportion of the population, and that cancer is predominantly a disease of the elderly, there is a fundamental need to develop primary, secondary and tertiary preventative strategies for delirium in these patients [19, 20]. Using early prophylactic strategies may reduce incident delirium, thereby reducing patient morbidity and mortality, [21] and suffering [22].

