### Sample size

There are varying viewpoints regarding the appropriate sample size for feasibility and pilot studies [54]. Whereas estimation may be guided on the basis of confidence intervals and standard deviation for continuous outcome measures, the situation is less clear in the case of pilot studies with time to event measures, such as time to onset of first incident episode of delirium. In inpatient palliative care settings, delirium incidence rates have been reported in the 3–45 % range [55]. In our main RCT, we anticipate a delirium incidence rate of approximately 25 % in the placebo arm by day 28 of admission. This would result in a 75 % administrative censoring proportion in the larger study. In addition, we arbitrarily set the anticipated proportion of noninformative censoring due to withdrawal or loss to follow-up at 10 %. We currently estimate a sample size requirement of *N* = 410 for the main study to detect an effect size (hazard ratio) of 0.5, given an alpha level of 0.05 and power of 80 %, using STATA version 14.1 (StataCorp LP, College Station, TX, USA) [56]. We further estimate that a sample size of 60 (arbitrarily set at approximately 15 % of the currently projected sample size of the larger study) with 30 participants in each arm will be adequate to provide useful data regarding the feasibility outcome measures.

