### Study drug and intervention protocol

The study medication tablets for both melatonin and placebo appear identical and are prepackaged in small blue containers labeled according to Natural Health Products Regulations and Good Labeling Practices. Both melatonin and matching placebo tablets have been manufactured and obtained from the same pharmaceutical company. Once prescribed by one of the PCU physicians, the dispensed container is sent to the unit by a pharmacy technician.

On study day 1 (D1), enrolled patients receive the study medication consisting of a tablet administered sublingually or via gastrostomy tube of either 3 mg melatonin (immediate-release) or placebo at 21:00 h (±1 h) until study day 28 (D28) of informed consent, or earlier in the event of death or discharge. In the event of incident delirium occurring before D28, the study drug is discontinued immediately. As standard practice on our unit, patients are assessed at the end of each 8-hour nursing shift with the Nursing Delirium Screening Scale (Nu-DESC) [59] to observationally screen for the presence of delirium. The Confusion Assessment Method (CAM) [58] is subsequently performed by a PCU physician as a confirmatory diagnostic test of delirium if Nu-DESC screening is positive.

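### Kaplan-Meier as the only time-to-event method overstates the share of patients who will have inpatient delirium, because death and discharge compete; a main trial sized on that figure could be too small

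*Protocol article*

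**What the plan says.** The Data analysis plan describes the analysis as mainly descriptive and adds: "we will also assess time to first episode of incident delirium with a Kaplan-Meier survival analysis". It names no other time-to-event method. It says that the pilot data will help to estimate the main trial's sample size, and names one statistic for this purpose, the upper one-sided 95 % limit of the median time to onset.

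The outcome is inpatient delirium only (Background; Primary objective). Under Study drug and intervention protocol, treatment runs to day 28 "or earlier in the event of death or discharge", and Withdrawals and discontinuation lists death and discharge again.

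The Sample size section says "we anticipate a delirium incidence rate of approximately 25 % in the placebo arm by day 28 of admission", and continues: "This would result in a 75 % administrative censoring proportion in the larger study". A further 10 % is set aside for "noninformative censoring due to withdrawal or loss to follow-up". The target is "to detect an effect size (hazard ratio) of 0.5", and the resulting N is 410. Death and discharge before day 28 have no place in this calculation.

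**The concern.** A patient who dies without delirium can no longer develop it, and a patient who is discharged can no longer develop it as an inpatient. Both are competing events. A standard Kaplan-Meier curve removes these patients from the risk set and in effect spreads later delirium risk over them. Its complement is therefore at or above the proportion who really have the event, and strictly above it whenever some patients die or leave before later delirium events. This is arithmetic and does not depend on how death and delirium are related.

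The independence that would give 1-KM a clear meaning is also doubtful here. The Background says that delirium occurrence rates above 80 % "have been reported in the last hours and days before death".

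At stake is the pilot's stated purpose of informing the main trial's size. The number of delirium events in that trial depends on the crude probability of the event. If 1-KM is entered in its place, too many events are expected and N comes out too small. The existing sizing has no term that would correct this.

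**Working it through.** **Step 1: reproduce the plan's N.** Inputs from the Sample size section are hazard ratio 0.5, control incidence 25 %, 10 % loss, and "given an alpha level of 0.05 and power of 80" %. Allocation is 1:1. The article does not state whether alpha is two-sided; two-sided reproduces its N.

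- Freedman events: (1.960 + 0.842)² × [(1 + 0.5)/(1 − 0.5)]² = 7.849 × 9 = 70.6, or 71 rounded up.
- Melatonin-arm incidence: 1 − 0.75^0.5 = 0.134. Mean over arms: (0.250 + 0.134)/2 = 0.192.
- N = 71/0.192/0.9 = 411 (409 with unrounded events). The stated 410 is reproduced. Schoenfeld's formula gives 382 and does not match.

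**Step 2: the pilot's 1-KM entered in the same formula.** Assumptions: true crude control incidence of 25 % by day 28; constant cause-specific hazards; a proportion q of controls who die or leave first without delirium. The article gives no q, so 30, 50 and 60 % are shown.

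- Total cumulative hazard: H = −ln(1 − 0.25 − q).
- Delirium share: A = H × 0.25/(0.25 + q). Competing share: B = H − A.
- 1-KM in controls: 1 − exp(−A). In the melatonin arm: 1 − exp(−A/2).
- N from these: 70.6/(mean of the two)/0.9.
- True melatonin crude incidence: (A/2)/(A/2 + B) × [1 − exp(−(A/2 + B))].
- True events E = N × 0.9 × mean crude incidence. Power = Φ(√E × (1 − 0.5)/(1 + 0.5) − 1.96) = Φ(√E/3 − 1.96).

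Worked at q = 50 %: H = −ln 0.25 = 1.386, A = 0.462, B = 0.924. 1-KM is 0.370 in controls and 0.206 with melatonin, mean 0.288, so N = 70.6/0.288/0.9 = 272. True crude incidence with melatonin is 0.137, so the mean is 0.1935. E = 272 × 0.9 × 0.1935 = 47.4, and power is Φ(6.89/3 − 1.96) = 63 %.

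| q | 1-KM in controls | N from 1-KM | True events | True power | N needed |
|---|---|---|---|---|---|
| 30 % | 30.4 % | 334 | 57.9 | 72 % | 407 |
| 50 % | 37.0 % | 272 | 47.4 | 63 % | 406 |
| 60 % | 42.8 % | 234 | 40.9 | 57 % | 404 |

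The last column shows that, when 25 % is crude, competing events barely change the N required and 410 is enough.

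**Step 3: the anticipated 25 % is itself a net (1-KM) figure.** Here the assumed rate is defined differently, as the probability of death or discharge by day 28 in the absence of delirium. Then A = −ln 0.75 = 0.288, B = −ln(1 − that probability), and crude control incidence = A/(A + B) × [1 − exp(−(A + B))]. N needed uses 71 events.

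| Death or discharge, absent delirium | Crude control incidence | N needed | Power at N = 410 |
|---|---|---|---|
| 20 % | 22.5 % | 456 | 76 % |
| 50 % | 18.3 % | 562 | 67 % |
| 80 % | 12.9 % | 802 | 52 % |

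**Step 4: the one named sizing statistic.** With 25 % by day 28 and an exponential curve, the median is 28 × ln 2/(−ln 0.75) = 67 days, well past day 28. Even the highest 1-KM in Step 2, 42.8 %, does not reach 50 %. The median and its upper limit are therefore probably not estimable, and sizing would have to use some other summary of the curve.

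**The case against.** Several stronger readings are tempting, and the article does not support them.

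- A reader might infer that the plan declares death and discharge to be noninformative. It does not. That word is applied only to withdrawal or loss to follow-up, and the article does not say how death and discharge enter the analysis. Censoring them follows from standard use of Kaplan-Meier.
- A reader might infer that the main trial will be undersized. N = 410 rests on an anticipated 25 %, not on a Kaplan-Meier estimate, and nothing commits the sponsor to putting 1-KM into the formula. The one named statistic, an upper limit of the median, points to a lower hazard and so a larger N. That stands as to direction, but Step 4 shows why it is a weak safeguard.
- A reader might infer that Kaplan-Meier is invalid here. Censoring competing events is proper for the cause-specific hazard and the log-rank comparison, and the main trial is sized on a hazard ratio. The error lies only in reading 1-KM as an event probability.
- The Background's statement about delirium near death cuts both ways. If most dying patients become delirious first, many deaths follow an event already counted, and death without delirium may be less common. It supports no particular value of q.
- Sampling error is large. A simple 95 % interval around 25 % is about ±15 points with 30 patients (1.96 × √(0.25 × 0.75/30)) and ±11 with 60. At q = 30 % the bias of about 5 points is smaller than that. It is nevertheless systematic and avoidable.
- The abstract and Background also plan incident rates and patient-days adjusted for length of admission. These supply other information on incidence but do not resolve the competing risk.

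**Conclusion.** The point holds in a limited form. For an inpatient-only outcome with death and discharge as expected endings, the single time-to-event method named yields a complement that overstates the proportion who will have the event, and the Sample size section leaves no room for these endings. Undersizing is possible rather than certain: it requires that 1-KM be used as the event probability, or that 25 % already be a net figure. If 25 % is crude, N = 410 is adequate.

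The power figures in Steps 2 and 3 rest on constant hazards and on death and discharge rates that the article does not give, so they show direction and order of magnitude only. The analysis is descriptive, in a 60-patient feasibility study not powered for efficacy, and no confirmatory conclusion depends on it. This is a worthwhile and inexpensive improvement, not a defect that must be cured before the study can proceed.

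**What to change.** In the Data analysis plan, state that delirium incidence by day 28 will be estimated with the Aalen-Johansen cumulative incidence function, with death without delirium and discharge without delirium as separate competing events, and that the day-28 proportion of each will be reported. State also that the main trial will be sized on this crude incidence, or on the cause-specific delirium hazard together with the death and discharge hazards, and not on 1-KM. In the Sample size section, say whether the anticipated 25 % is a crude or a net figure. Kaplan-Meier with these events censored may stay for the cause-specific hazard and the log-rank comparison.

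The cost is wording and a little more analysis. Death and discharge already end study treatment, so their dates should be on record, and the trial was still recruiting when the article was written. The projected N for the main trial may rise.

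### At the plan's own 25% day-28 delirium incidence, the upper confidence limit of the median time to onset will almost certainly not be estimable, so the day-28 probability should be used to guide the main-trial sample size

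*Protocol article*

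**What the plan says.** Two sections of the protocol article bear on this.

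- **Sample size.** For the main trial, "we anticipate a delirium incidence rate of approximately 25"% "in the placebo arm by day 28 of admission". The article continues: "This would result in a 75"% "administrative censoring proportion in the larger study". Withdrawal or loss is set at 10%. The main trial needs N = 410 "to detect an effect size (hazard ratio) of 0.5" with alpha 0.05 and 80% power. The feasibility study takes 60 patients, 30 per arm. Published inpatient incidence is given as 3-45%.
- **Data analysis plan.** The analysis is mainly descriptive. Time to first delirium is assessed by Kaplan-Meier, and the upper one-sided 95% "limit of median time to onset will also be derived to further guide sample size considerations for the full randomized trial". No parametric model is named, and nothing is said about a median that is not reached.

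Study drug is given to day 28, or stops earlier at death or discharge (Study drug and intervention protocol). Table 1 schedules delirium screening over the same 28 days.

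**The concern.** A Kaplan-Meier median exists only if the estimated curve falls to 0.5 within follow-up. Its upper confidence limit exists only if the upper confidence band also falls to 0.5, which takes clearly more than half the patients having the event. The Sample size section expects a quarter of the placebo arm to have it, and fewer on melatonin if the drug works. The statistic chosen to guide the main trial therefore does not fit the figures the main trial is planned on.

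The median is also not the quantity that drives N = 410, which depends on the probability of an event by day 28. If the median limit is reported as not reached, a replacement has to be chosen after the data have been seen.

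**Working it through.** **Inputs (Sample size section).** Placebo day-28 incidence 0.25; hazard ratio 0.5; alpha 0.05, read as two-sided; power 80%; withdrawal 10%; 30 patients per arm.

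**1. Reproduce N = 410.**
- Melatonin day-28 incidence: 1 − 0.75^0.5 = 0.134.
- Mean event probability: (0.25 + 0.134)/2 = 0.192.
- Freedman log-rank events: (1.960 + 0.842)² × (1.5/0.5)² = 7.849 × 9 = 70.64.
- N = 70.64/0.192/0.9 = 409. Rounding events up to 71 gives 411.

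This reproduces 410. The Schoenfeld formula (66 events) gives 383 and does not. What drives N is the day-28 event probability; no median enters.

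**2. Expected pilot events.** 30 × 0.25 + 30 × 0.134 = 7.5 + 4.0 = 11.5 of 60 before withdrawal. The curves should end near 0.75 (placebo), 0.87 (melatonin) and 0.81 (pooled).

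**3. Chance that the median is reached, no early censoring (exact binomial).**
- At least 15 of 30 at 25%: 0.27%.
- At least 30 of 60 at 25%: 0.003%.

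**4. Events needed for a finite upper limit.** The condition is S + 1.645 × √(S(1 − S)/n) ≤ 0.5.
- n = 30: 19 events give 0.367 + 0.145 = 0.511 (fails); 20 events give 0.333 + 0.142 = 0.475 (passes).
- n = 60: 36 events give 0.400 + 0.104 = 0.504 (fails); 37 events give 0.383 + 0.103 = 0.487 (passes).
- Log-log limits need the same counts.
- At 25% incidence, P(at least 20 of 30) = 1.8 × 10⁻⁶ and P(at least 37 of 60) = 2 × 10⁻⁹.

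**5. Simulation with early censoring.** 5,000 pilots per scenario, exponential times, follow-up cut at day 28. Early-exit proportions above the stated 10% are assumptions.

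| n | Day-28 incidence | Leave early | Median reached | Upper limit finite |
|---|---|---|---|---|
| 30 | 25% | 10% | 0.3% | 0 |
| 60, HR 0.5 | 25% placebo | 10% | 0 | 0 |
| 30 | 25% | 73% | 2.7% | at most 0.04% |
| 30 | 25% | 80% | 3.9% | 0.04% |
| 30 | 25% | 95% | 10% | at most 0.06% |
| 30 | 45% | 10% | 28% | about 1.8% |
| 60 | 45% | 10% | 22% | about 1% |
| 30 | 45% | 80% | 35% | 2.1-2.5% |

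**6. What is estimable at the same inputs (no early censoring).**
- Placebo arm, n = 30: incidence 0.25, one-sided 95% lower limit 0.25 − 1.645 × √(0.25 × 0.75/30) = 0.12.
- Pooled, n = 60: incidence 0.192, lower limit 0.192 − 1.645 × √(0.192 × 0.808/60) = 0.108.

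**The case against.** **The statistic is an addition.** The Data analysis plan says that recruitment, retention, protocol-violation and time-to-onset data together will assist sample-size estimation. The Kaplan-Meier curve it already plans shows the day-28 probability directly. A reader might infer that the pilot will deliver nothing for sizing the main trial. The article does not support that, and this part of the objection stands in full.

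**The 25% may be a crude proportion.** These are palliative inpatients, and follow-up can end at death or discharge. If 25% is the crude share with delirium and many others leave early, the Kaplan-Meier incidence is higher: about 40% if 80% in total have had delirium or left by day 28, and about 55% if 95% have. Simulating net risks of 45-55% with 80-90% leaving early (assumptions that give about 24-25% crude events), the median is reached in about 35-57% of 30-patient arms. The upper limit is still finite in only about 2-6% of them, and in about 9% of 60-patient samples at 55% and 90%. It reaches 18-30% of 60-patient runs only at net risks of 60-65% with 90% leaving early. This reading fits poorly with a stated 75% administrative censoring. It weakens the figures for the median but not the conclusion on its limit.

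**A parametric median could be computed.** An exponential model at 25% gives 28 × ln 2/(−ln 0.75) = 67 days. That is well outside the 28-day window, and the article names only Kaplan-Meier.

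**The detail may sit in an analysis plan not shown.** The point is not an omission: the article itself fixes this statistic.

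**Conclusion.** The concern holds for this one statistic. At the plan's own inputs the Kaplan-Meier median will very probably not be reached: about 0.3-0.4% of 30-patient arms, or about 3% if roughly 70% leave early. Its upper one-sided 95% limit will essentially never be finite, and is so in only about 2% of pilots at 45% incidence. This rests on reading 25% as the net day-28 risk, in line with the stated 75% administrative censoring, and on constant hazards in the simulations. Under the crude reading the upper limit remains unlikely.

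Two stronger readings should be resisted. One is that the limit cannot exist at all: it can, with small probability, and 25% is an anticipated value that the pilot is there to test. The other is that the flaw undermines the feasibility study or N = 410. The study is mainly descriptive, its primary objectives do not depend on this limit, and 410 reproduces. This should be fixed, but nothing else in the study hinges on it.

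**What to change.** In the Data analysis plan, replace the median limit with the Kaplan-Meier probability of first incident delirium by day 28, in the placebo arm and pooled over arms, each with a one-sided 95% lower confidence limit for incidence. That keeps the cautious direction of the planned limit: slower onset means fewer events and a larger trial.

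State which of these estimates enters the log-rank formula behind N = 410, since the placebo and pooled limits lead to different sample sizes. If the estimate is Kaplan-Meier, inflate for withdrawal once. If it is a crude proportion, patients who withdrew before an event are already in the denominator, so do not inflate again.

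The cost is a sentence or two. No extra data, visits or patients are needed, and the change can be made before the data are analysed.

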## Discussion

We have chosen to limit the study participants to those with a cancer diagnosis, as a heterogeneous study sample with a variety of life-threatening illnesses could conceivably make it more difficult to achieve a good balance in the two study arms and thus lead to confounding. Our study will include patients with dementia, which is one of the strongest predisposing risk factor for the development of delirium, along with advanced age. Although this will generate some challenges in the assessment of delirium superimposed on dementia, we postulate that those with dementia may well be the group that is most likely to benefit from melatonin.

We have chosen to implement the “Canadian guidelines on the assessment and treatment of delirium in older adults at the end of life” [26] as part of this feasibility study. We do not anticipate that this will interfere with any data analysis, as the implementation of these guidelines will be consistent for all randomized study patients and all inpatients on the PCU. As part of our feasibility study, we are piloting standardized checklists that were designed to comprehensively and systematically capture data regarding predisposing risk factors for delirium at admission (through the BRP-DICT form) and precipitating factors for delirium in the 24 h post delirium diagnosis (through the PP-DICT form).

The research nurse and research assistant are documenting field notes during this study, thus adding a qualitative component to this study. These “lessons learned” will provide additional insights into the potential barriers and feasibility of subsequent studies. The outcomes of this feasibility study will provide information on recruitment and retention rates, protocol violation frequency, effectiveness of the blinding process, acceptability of the study procedures and safety of the proposed intervention. This will inform the design of a fully powered RCT to evaluate the preventative role of melatonin administration in patients with advanced cancer.

